# TREATMENT OF SUBJECTS

*intervention studies>*

## Investigational product/treatment

The intervention in this study is based on current evidence. It was developed further in close collaboration with two FPs of our project team and two FPs participating in the study.

The intervention will contain the following elements:

1. Cognitive classification of all elderly patients.

Aimed to increase FPs’ awareness of cognitive dysfunction and dementia in their patients FPs are asked to explicitly classify cognitive function in all their patients above the age of 65, based on their recollection and if needed the medical records. They did a (cross-sectional) classification of the cognitive function of their entire elderly practice population. They could classify patients as: ‘probable dementia’; ‘possible cognitive impairment or dementia’; ‘no signs of cognitive impairment’ or ‘not in sight’. The intervention targets the group classified as possibly cognitively impaired.

During the course of the trial FPs will adjust the classification of patients’ cognitive status when needed. They will record this in the medical records.

2. Training of FPs and practice nurses.

In order to improve diagnosis and management of dementia in primary care, FPs and practice nurses will undergo a training that was part of an effective intervention recently develop by Perry et al.(Perry et al. 2008). The training focuses on collaboration between FPs and practice nurses in diagnosing and managing dementia. FPs will consider barriers to dementia diagnosis and will learn how to diagnose dementia according to current guidelines (particularly the dementia guideline of the Dutch College of General Practitioners). Additionally differential diagnosis and pharmacological treatment of dementia are considered.

In order to improve care for elderly, possibly cognitively impaired patients, practice nurses will learn how to work with the RAI instrument, a standardised instrument for broad functional assessment of elderly patients and their informal caregiver. In addition, they will learn how to make a care plan and evaluate it periodically. The RAI instrument also provides protocols for clinical analyses of identified problems, supporting the formulation of an adequate care plan.

3. The deployment of a practice nurse.

An extra practice nurse who exclusively focuses on the group of patients with possible cognitive impairment is deployed in the intervention practices. She will work with the instruments mentioned above to assess care needs of both the patient and the primary informal caregiver. She will prioritise problems and prepare a care plan in consultation with the informal caregiver. Next, she will share the results with the FPs and finalise the care plan in close collaboration with the FP. For a graphic overview of the intervention see appendix 1.

Additionally, as we expect to identify dementia in a substantial proportion of patients, she will gain expert knowledge on all dementia services in the region and establish close collaboration with secondary care providers. The practice nurse will serve patients of several PCPs. She will be supervised by one of the FPs participating in the study. The practice nurse will have patient contacts according to a predefined schedule; Agreements are made with FPs that they remain responsible for all medical care, including crisis management during the study. Appendix 1 provides an overview of the intervention.

4. Structured collaborative care in the region.

In the region several secondary care providers are involved in dementia care: a) a nursing home recently begun deployment of case managers for home-dwelling dementia patients. b) There is an academic memory clinic and there are two geriatric outpatient clinics that FPs frequently refer to.

We aim to make agreements on collaboration between FPs and these providers based on the outlines for this in the National Collaboration Agreement for primary dementia care. These include for example agreements on information exchange, prescription of drugs, consultation and referral, crisis situations, (crisis-) admission.

The nursing home is planning to organise multidisciplinary expert team meetings. We aim to make agreements about consultation of this expert team by the practice nurses.

**Usual care**

In the usual care group FPs were also asked to explicitly classify cognitive function in all their patients above the age of 65, based on their recollection and if needed the medical records. They will also adjust this classification in the course of the study. No other interventions will be done.

Usual care for the group of patients consists of normal care as provided by FPs.

The literature shows that there is a number of barriers to dementia diagnoses in primary care(Bradford et al. 2009). We therefore expect FPs in the usual care group to be more reluctant to diagnose dementia, additionally because they have less subsequent to offer compared to the intervention group.

When they do proceed to diagnose dementia they will likely do this according to the guideline on dementia of the Dutch College of General Practitioners and when dementia is suspected in the majority of cases FPs will refer patients for further diagnostic evaluation. Follow-up care consists of referral to home care services and possibly more specific services for dementia patients in the region. In general a structured assessment of care needs is not performed nor is a comprehensive care plan made. In a minority of practices, there is a practice nurse for the elderly present. In those practices, structured assessment of care needs of elderly patients and development of a care plan is more likely to occur.

In usual care, there are no explicit agreements on collaboration and referral among care providers in this region.

## Use of co-intervention (if applicable) not applicable

## Escape medication (if applicable) not applicable

##

# INVESTIGATIONAL MEDICINAL PRODUCT

Not applicable

# METHODS

## Study parameters/endpoints

The primary outcome of this study is quality of care. Previous research on the effects of an educational intervention combined with coaching of PCPs and practice nurses demonstrated a positive effect on some elements of quality of care(Perry et al. 2008).

### Main study parameter/endpoint

The primary outcome is quality of care: quality of the diagnostic process and subsequent care is measured by a set of 23 QIs (Perry et al. 2010). **Appendix 2** provides an overview of these QIs.

### Secondary study parameters/endpoints (if applicable)

Patient and caregiver wellbeing and cost-effectiveness:

**Appendix 3** provides an overview of caregiver and patient outcomes and potential effect modifiers measured. There is no information on cost-effectiveness of this type of interventions. Therefore we will also measure health care utilisation of both the patient and the caregiver, including time till institutionalisation of the person with dementia. In order to assess a long term effect we will follow patients and their informal caregivers for the period of three years.

Diagnostic accuracy study: the FPs cognitive classifications ‘possible cognitive impairment/dementia’ and ‘no signs of cognitive impairment’ are compared to the CAMCOG diagnosis on the presence or absence of dementia or MCI.

Feasibility of the intervention:

The level of implementation will be measured. For this the PN will record all her activities in a diary; additionally medical records are used.

Success and failure factors of the intervention at different levels will be derived from (2) focus groups with FPs and PNs. Additionally semi-structured interviews will be conducted with 5 persons with dementia and their informal caregiver, in order to also include the patient perspective.

### Other study parameters (if applicable)

## Randomisation, blinding and treatment allocation

We will use prognostic stratification before randomisation. Each primary care practice will be stratified based on the two most important potential effect modifiers. Based on previous research of Perry et al. these are a) whether FPs collaborate with a practice nurse and b) the percentage of elderly patients within practices.

**Figure 2** provides an overview of the patient flow of the cluster RCT.

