**Setting and Study population:**

The cluster RCT is executed in 16 primary care practices (PCPs) among 312 patients ≥ 65 years in whom FPs suspect cognitive impairment.

The diagnostic accuracy study is executed among 312 patients labelled ‘possible cognitive impairment’ and in 100 patients labelled ‘no signs of cognitive impairment’ by FPs.

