## Multivariate analysis

We will do multilevel multivariate analysis to compare the two care conditions controlling for baseline imbalance and clustering effects within practices on number of incident diagnoses (goal 1), quality of care (goal 2) patient and caregiver outcomes (goal 3). Effect modification will be explored on principal characteristics (age, gender, severity dementia and type of caregiver). A post hoc analysis on main outcomes will be done on patients who score under critical cut off on CAMCOG at baseline (<86).

In addition, an economic evaluation is performed from societal perspective comparing the effects of goals 1 to 3 and costs in the two conditions. To compare costs between the two groups, confidence intervals for the differences in mean costs are calculated using bias-corrected and accelerated bootstrapping with 5000 replications. For the cost-effectiveness analysis the difference in total costs between the intervention and usual care group are compared with the difference in main clinical outcomes.

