**Appendix 3. Overview of caregiver and patient outcomes and potential effect modifiers**

| *OVERVIEW* | Instrument | Items | Form | Time min | T0 | T1 | T2 | T3 | T4 |
| --- | --- | --- | --- | --- | --- | --- | --- | --- | --- |
| *Outcomes caregiver* |  |  |  |  |  | 6 m | 12m | 18m | 24m |
| Burden | SSCQ | 12 | I | 10 | X | X | X | X | X |
| QoL | MDS* & EQ5D |  | Q | 20 | X | X | X | X | X |
| Psychopathology | GHQ12 | 12 | I | 10 | X |  | X |  | X |
| Care utilisation, care time and absenteeism | MDSe* / cost diary |  | Q/I | 15 | X | X | X | X | X |
| *Outcomes pt* |  |  |  |  |  |  |  |  |  |
| Presence of dementia / MCI | CAMCOG1 |  | I | 25 | X |  | X |  |  |
| QoL | QoL-AD & EQ5D | 16 | I | 15 | X | X | X | X | X |
| Care utilisation etc. | MDSe* / cost diary by porxy |  | Q/I | 0 | X | X | X | X | X |
| Time until nursing home admission | According to carer or PCP | - | I |  |  |  | X |  | X |
| *Potential effect-modifiers / confounders* |  |  |  |  |  |  |  |  |  |
| Carer: |  |  |  |  |  |  |  |  |  |
| Sociodemography | MDS | 5 | I |  | X |  |  |  |  |
| Social support  Duration and intensity of caring | SSSL  Added Q | 8  1  1 | Q  I |  | X  X |  | X |  | X |
| Patient: |  |  |  |  |  |  |  |  |  |
| Sociodemography | By proxy | 5 | I | 5 | X |  |  |  |  |
| Dementia type | Medical Records | 1 | I | 0 |  |  | X |  |  |
| Morbidity | MDS by proxy | 1 | I | 5 | X |  |  |  |  |
| Behavioural symptoms | NPI | 12 | I | 10 | X |  | X |  | X |
| PCP / primary care practice:  - Age  - Sex  - Presence of practice nurse for elderly patients  - Interested in dementia  - % patients ≥ 65  - Cluster size | Q  Q  Added Q  Added Q  Medical rec | 1  1  1  3 | Q  Q  Q  Q |  | X  X  X  X  X  X |  |  |  |  |

I=Interview

Q=Questionnaire

MDS* / MDSe*: Minimal DataSet / Minimal DataSet cost-effectiveness respectively (NPO-ZonMW).

1 intervention arm only

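### The effect-modifier list in section 9.3 omits both practice factors that section 7.2 stratifies on as the most important potential modifiers, and the nurse factor is worded two ways

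*Protocol*

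**What the plan says.** Four places in the protocol bear on this point.

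- **Section 7.2 (Randomisation, blinding and treatment allocation):** "Each primary care practice will be stratified based on the two most important potential effect modifiers". Citing previous research, it gives these as "whether FPs collaborate with a practice nurse and b) the percentage of elderly patients within practices".
- **Section 9.3 (Multivariate analysis):** the two care conditions are compared in a multilevel model "controlling for baseline imbalance and clustering effects within practices". Then: "Effect modification will be explored on principal characteristics (age, gender, severity dementia and type of caregiver".
- **Appendix 3:** under the label "Potential effect-modifiers / confounders" it lists practice variables taken at T0. They include the percentage of patients aged 65 or over and "Presence of practice nurse for elderly patients".
- **Section 5.1 (Usual care):** "In a minority of practices, there is a practice nurse for the elderly present". It adds that structured needs assessment and care planning are more likely in those practices.

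**The concern.** The protocol identifies two practice characteristics as the likeliest sources of varying effect, builds the randomisation on them and plans to record them. It then writes a list of modifiers that leaves both out and consists only of patient and caregiver characteristics. What a protocol merely leaves to a statistical analysis plan would not be worth raising. Here the protocol itself writes the list, and the list does not match its own statement of what matters most. An analysis plan built from section 9.3 would carry the omission forward, and adding the factors after the data are seen would look data-driven.

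The question has practical weight. A core element of the intervention is an extra practice nurse (section 5.1, element 3), so a reader will ask whether it adds less where a nurse is already involved. Several of the scored indicators in Appendix 2 cover the same activities that the usual-care text links to a nurse for older patients: needs assessment (indicators 8 and 9) and care plans (14 to 16).

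The two wordings of the nurse factor add to the difficulty. If they mean different things, a practice could sit in one category for stratification and another in the data set. An interaction would then have two possible definitions with no rule for choosing between them.

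**Working it through.** **1. The sections side by side**

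| Factor | Section 7.2 (stratifier) | Appendix 3 (collected at T0) | Section 9.3 (modifier list) |
|---|---|---|---|
| Nurse | collaboration with a practice nurse | practice nurse for older patients present | not listed |
| Share of elderly patients | yes | yes | not listed |
| Patient age, patient sex, dementia severity, caregiver type | no | not compared here | listed |

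The parenthesis in section 9.3 has no wording that marks it as a set of examples. The model sentence mentions baseline imbalance and clustering but does not name the stratification factors. Section 7.2 also calls its stratification prognostic while describing the factors as effect modifiers. These are different properties, and the wording could be tidied at the same time.

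**2. What adding the nurse interaction could deliver**

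The protocol gives no figure for an interaction, so there is none to reproduce.

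Inputs from the protocol:
- 16 practices and 312 patients ("The cluster RCT is executed in 16 primary care practices (PCPs) among 312 patients"); 8 practices per arm (Figure 2). Patients per practice m = 312/16 = 19.5.
- Section 4.4: within-practice SD 35, between-practice SD 3, target difference 22.5 points.

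Assumptions: a = 2 to 4 nurse practices in each arm (the protocol says only that a minority have a nurse for the elderly), equal practice sizes and no loss to follow-up.

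As a check on the inputs, the cluster formula at m = 14 gives 4.006 practices per arm for 90% power. Rounded up, that is 5 practices and 70 patients per arm, close to the protocol's 5 and 72.

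Variance of a practice mean: v = 3² + 35²/19.5 = 9 + 62.8 = 71.8.

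Main effect: SE = √[v(1/8 + 1/8)] = √(71.8/4) = 4.24 points. Power for 22.5 points is 99.8% (t, 14 df).

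Interaction of arm with a yes/no practice factor: the four cells hold a, a, 8−a and 8−a practices, so SE = √[v(2/a + 2/(8−a))], with 16 − 4 = 12 df.

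| Nurse practices per arm | SE (points) | 95% CI half-width | Power, 11.25 points | Power, 22.5 points | Detectable at 80% power |
|---|---|---|---|---|---|
| 2 | 9.8 | 21.3 | 18% | 56% | 29.9 |
| 3 | 8.8 | 19.1 | 22% | 66% | 26.8 |
| 4 | 8.5 | 18.5 | 23% | 68% | 25.9 |

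Even with an even split (a = 4), the interaction's SE is √v against √(v/4) for the main effect, twice as large. If the between-practice SD were 7 to 10 instead of 3 (assumed range), power for a 22.5-point interaction falls to 29% to 50%, and the size detectable at 80% power rises to about 32 to 45 points.

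**The case against.** The strongest reply is that little is lost. Section 9.3 promises only exploration. Appendix 3 collects a nurse variable and the elderly share at T0 under a heading that names them as possible modifiers, so both can still be examined. Power would be poor, as the table shows. On the nurse wording, section 7.2 does not say what kind of practice nurse it means, and no section describes a practice that has one kind but not the other, so the shorter phrase may be shorthand.

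Much of this stands. The wording of the nurse factor is an ambiguity to resolve, not a proven conflict. The interactions will be imprecise. But low power applies to every practice-level question in this trial, and it does not explain why the two factors called most important are left off a list that names four others.

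A reader might go further in two ways that the document does not support.

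- **That the trial will therefore fail to show where the intervention works.** The variables are collected, so the question stays open to analysis. Adding the interactions would not settle it either, given their precision.
- **That stratifying on one nurse wording leaves the other unbalanced and biases the primary comparison.** The protocol gives no number of practices with such a nurse, no size for that nurse's effect on the quality score and no link between the two wordings. Appendix 2 measures the indicators at baseline, and section 9.3 adjusts for baseline imbalance, which should absorb at least part of any pre-existing difference.

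**Conclusion.** The point holds as an internal inconsistency with a cheap remedy. Section 9.3's list of modifiers omits both factors that section 7.2 names as most important and that the randomisation uses. The nurse factor is worded one way in section 7.2 and another in Appendix 3 and the usual-care text. The omission rests on the text alone and needs no assumption.

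The consequence is limited to an exploratory analysis. Neither the sample size nor the validity of the primary comparison is in question. What the correction buys is a pre-specified estimate with a confidence interval of roughly ±18 to ±21 points for the nurse interaction. That figure depends on the protocol's between-practice SD of 3 and on 2 to 4 nurse practices per arm, and a larger SD would widen it.

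**What to change.** In section 9.3:
- Include both stratification factors, as used at randomisation, as covariates in the multilevel model.
- List both as pre-specified exploratory treatment-by-factor interactions, reported as estimates with confidence intervals.

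In section 7.2 and Appendix 3:
- State one definition of the nurse factor, or state that two different variables are intended.
- If practices are already randomised, keep the stratifier as it was used and report the Appendix 3 variable separately. The stratifier should not simply be replaced, because its stated basis is previous research that the protocol does not reproduce.

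The cost is a few sentences. No new data collection is needed beyond retaining the stratum assignments. With one parameter each, the two covariates use two of the 14 practice-level degrees of freedom. The number of exploratory interactions rises from four to six. The main drawback is imprecision: with 16 practices, only a nurse interaction of about 26 to 30 points is detectable with 80% power on the protocol's SDs. The text should say that these analyses are exploratory and that a wide interval is not evidence of a uniform effect.

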## Study procedures

Subjects will not undergo any new or experimental treatment in the course of this study. Their providers will be trained to deliver care (both the process of diagnosis, disclosure and psychoeducation and the process of follow-up care management and support) in closer concordance with current guidelines. Care will become more structured both at the level of the PCP and within the region. For the subjects this will presumably result in an earlier and more thorough assessment of their care needs and earlier intervention or referral. No subjects will be withheld from treatment. We aim to introduce the intervention also in the control group. Because of feasibility the intervention will be introduced in this group one year later.

*Eligibility*

The researchers will assess eligibility of all patients for the study that were diagnosed with dementia. Before approaching potential participants, FPs will go through the list of potential participants to see whether there are any other contraindications, besides the predefined exclusion criteria, to study participation of these persons.

*Recruitment*

Subjects will be informed about the study by means of an invitational letter from their FP and an information leaflet with detailed information about the study: aim of the study, what participation means for participants, freedom to not participate or to end participation at any time without having to give a reason, etc. Subjects are encouraged to discuss the matter with friends or relatives or with their FP. Some subjects may not want to be contacted about the study. They can communicate this by returning a form by post: on this form subjects can indicate that they are not interested to participate in the study and that they do not want to be contacted. A return envelope is provided. (letter and information leaflet are added to this protocol as separate documents)

If subjects do not object, they are contacted by telephone by one of the researchers. Additional clarification about the study is provided, if needed. Subjects are asked whether they are interested to participate in the study. If this is so, an appointment will be made for obtaining informed consent and for the baseline interview.

*Informed consent*

Informed consent will be obtained for participation in the questionnaire and interview part of the study. Informed consent is obtained both from the person with possible cognitive impairment as from the caregiver. If persons are not capable to give informed consent themselves, a legal attorney will be asked to give informed consent on their behalf. People with possible cognitive impairment are considered incapable of giving informed consent if they are not capable to reproduce the goal of the study and what it would mean for them to participate.

*Interviews and questionnaire*

Structured interviews are conducted by trained interviewers. For this patients and caregivers will be visited at home half yearly. The questionnaires for informal caregivers are posted one week in advance to the home visit for the interview. Caregivers are asked to fill in the questionnaire within this period so that the interviewer can collect the questionnaire when visiting.

*Care utilisation diary*

Caregivers are asked to record the formal and informal care use of the one they are caring for. This will be checked and if necessary supplemented during the 6 monthly interviews.

*Process evaluation*

*General approach:* We apply the approach for process evaluations for implementation of care innovations of Meiland et al. 2005. Meiland’s approach of adaptive implementation distinguishes (external) factors that throughout the process affect the implementation such as characteristics of the intervention, preconditions for the intervention, human and financial resources. Also during the various stages of implementation various factors can play a role, namely during preparation, the introduction and the continuation phase. Within each phase distinction is made between micro level (patient / caregiver and individual worker), meso level (between and within care organizations) and macro level (legislation, financing context).

To give an impression at the micro level questions will be asked such as:
(i) To what extent are the health needs identified early and properly diagnosed according to carers? (ii) To what extent can adequately respond to identified health needs? (iii) Has the coordinated dementia care a value according to the user?
The exact number of interviews is determined by the point of saturation of information is reached (saturation). The interviews are recorded, analyzed and uncertainties are checked with the respondents for validation.

*Practical approach:* To gain more insight in the feasibility of the intervention at the level of the primary care practice and in the context of regional elderly/dementia care providers, discussions with FPs and local care providers will be organized. Additionally a focus group with FPs and practice nurses will be held during the course of the project in order to further explore success and failure factors of the intervention. To get insight into failure and success factors on a regional level in addition key representatives of local care providers/services are interviewed.

We will also conduct semi-structured interviews with 5 random couples of persons with possible cognitive impairment and their informal caregivers in order to get a view of their experiences with the new form of care.

*Analytical approach:* The interviews are transcribed verbatim and all material is written using a qualitative analysis program analysis. The texts are encoded by two independent researchers based on the theoretical model. Differences in coding between the researchers discussed until agreement is reached. Then the per code excerpts and summarized in matrices described (Miles & Huberman, 1994). On this basis, facilitating and impeding factors for the introduction of integrated care and empowerment are described and recommendations for further implementation activities.

